### Study design

This exploratory sequential mixed-methods study will be divided into three phases, which are described below. Table 2 shows the enrollment, interview, intervention, and assessment schedule. This protocol was developed and reported in accordance with the Standard Protocol Items: Recommendations for Interventional Trials (SPIRIT), and the clinical trial will be carried out and reported in accordance with the Consolidated Standards of Reporting Trials (CONSORT). A visual diagram of the study process is shown in Fig. 1.

**Table 2 Tab2:**
[figure not shown]
Schedule of enrolment, interviews, intervention, and assessment of the Educational Intervention trial, following the Standard Protocol Items Recommended for Clinical Trials (SPIRIT) guidelines

**Fig. 1 Fig1:**
[figure not shown]
Study visual diagram

### Phase 1: the qualitative exploration

The qualitative study will take 5 months to complete. To explore the educational and learning needs of at-risk women, semi-structured interviews with open-ended questions and conventional qualitative content analysis methods will be used. The interviews will take place face-to-face in a mutually convenient quiet environment. In accordance with the study’s goals and objectives, an interview guide has been created. The first question is a wide, open-ended question about the participant’s feelings about STIs, to which they will be asked to respond in detail. Then, based on this response, further probing questions are asked. The goal is to gain a comprehensive understanding of women’s attitudes toward STIs. Each interview will be transcribed word by word immediately after each interview. The transcript will then be sent to each woman, along with a summary of key points extracted from each interview, to ensure that the interviewer has correctly interpreted their declarations (member checking), and any vague discrepancies will be resolved. In addition, we will use the literature review to identify the educational and learning needs of women about STIs in order to gain an understanding of their needs. Finally, an educational intervention that best fits the qualitative study results will be developed using the two approaches mentioned above (interview and literature review) and the ISD model.

### Phase 2: designing the intervention program

The second phase of the study begins after the required data has been collected through qualitative research. The purpose of this step is to develop an effective educational program based on the ISD model to promote preventive behavior from STIs among Iranian women.

### Conceptual framework of content development based on ISD model

Dick and Carey’s (2014) Instructional System Design (ISD) model provided the framework for this program. The ISD model depicts the processes and steps we take to effectively organize all components in order to achieve our objectives [34]. This model is a systematic and structured process that establishes a strong connection between stimulus (learning materials) and response (learning) [35]. The role of the environment in learning is highlighted in this systematic approach. According to this model, it is necessary to first identify the sub-skills that learners should master before selecting the stimulus and strategy that are appropriate for each sub-skill [36].

### Instructional System Design (ISD) model steps

#### The ISD includes 10 steps

Identify instructional goalsThe first stage determined what learners could accomplish after completing the educational process [37]. These objectives are the result of need assessments. Need assessments are analyses of the gap between one’s current status and one’s desired status.Conduct instructional analysisWhen learners have achieved their instructional goals, what they should do is determined by stages in a hierarchy.Analyze learners and contextsIn this stage, we will analyze learners’ STI learning experience, preferences, traits, and learning situations.Write performance objectivesWhen students complete the education program, they develop a detailed action plan based on the knowledge they have gained, which is aligned with performance objectives.Develop assessment instrumentsAssessment tools determine whether or not students met their objectives.Develop instructional strategyThe researcher determines the educational method that learners will use to achieve their ultimate learning goals during the educational strategy phase.Develop instructional materialsThe researcher will choose educational materials at this stage based on the instructional strategy.Design and conduct formative evaluationAt this stage, the educational content will be made available to at least 5 to 10 women outside of the research team, and the content’s validity will be evaluated in terms of applicability, comprehensibility, simplicity, and attractiveness.Design and conduct a summative evaluationFollowing the evaluators’ comments in Step 8, any possible and necessary corrections to the educational content will be made.Final evaluationThe effect of the intervention will be evaluated at this stage in three time periods: immediately, 1 month, and 3 months after the end of the educational intervention.

### Phase 3: the randomized controlled trial

Randomized controlled trials (RCTs) are the most effective way to assess public health interventions. RCT reduces the impact of confounding bias because each study participant is assigned to an intervention or control group solely by chance [38]. Figure 2 depicts the flow chart of the randomized controlled protocol.

**Fig. 2 Fig2:**
[figure not shown]
The flow chart of the randomized controlled protocol

### The intervention programs

The intervention will be created using the qualitative study’s phase 1 findings. Women who meet the inclusion criteria will be recruited indefinitely until the required sample size is reached. At this point, all participants will be coded and blindly allocated into one of the intervention and control groups by the researchers using a permuted block randomization program: (1) intervention (2) control.

Based on the design of the randomized controlled trial intervention, the impact of the intervention program on promoting women’s STI prevention behaviors will be assessed. Measurements will be taken at baseline, after one month, and after three months of following their respective program, as shown in Fig. 1. In accordance with ethical principles, the participants in the control group will also receive the most effective intervention after the final evaluation and comparisons of the three intervention groups.

### Strategies to improve adherence to interventions

Women are required to be present at the study site in person to receive the intervention, and any missed sessions are recorded to check adherence. To improve adherence, training program times are flexible between 9am and 5pm each day (room availability permitting), are not required to be at the same time of day, and are not required on weekends. Participants will be arranged for a free visit with a trained midwife for genital examination and health counseling.

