### Trial design

The evaluation design is a parallel, randomized controlled trial, with two arms and with a 1:1 allocation ratio. The intervention arm will receive the training program starting in June 2022, and the control arm will receive the training program after the final research data collection, with training from June 2023. If the trial is not able to recruit 63 women within the recruitment period, then the research team will consider an unequal allocation ratio with a smaller number of participants in the control group or extending data gathering time. The impact of this is discussed in the section on sample size.

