### Outcome measures

The initial research questions addressed in this study are “Does the educational intervention based on Instructional System Design (ISD) model affect STI preventive behaviors among Iranian women?”. To answer this main question following primary outcomes are expected:Determining and comparing the effects of an educational intervention designed based on the ISD model in STI knowledge among women in the target and control groups before, immediately one month, and three months after the interventions.Determining and comparing the effects of an educational intervention designed based on the ISD model in STI vulnerability among women in the target and control groups before, immediately, one month, and three months after the interventions.Determining and comparing the effects of an educational intervention designed based on the ISD model in STI prevention self-efficacy among women in the target and control groups before, immediately, one month, and three months after the interventions.Determining and comparing the effects of an educational intervention designed based on the ISD model in STI prevention intentions among the target and control groups before, immediately, 1 month, and 3 months after the interventions.

Consequently, we expect the effect of our educational intervention on preventive action regarding STIs among women. To assess the expected secondary outcomes a self-reported assessment addressing preventive actions (using a condom, doing pap-test and genital examination) will be conducted.

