### Engagement and retention

As this is a group of participants that can be particularly difficult to participate and maintain in a study, given the sensitive nature of STIs, several steps will be taken to optimize retention. These include scheduling training at maximally convenient times for participants, hiring a trained midwifery that will be flexible and attentive to the individual’s needs, and frequent opportunities for questions and feedback. In addition, for a free visit, a trained midwifery will coordinate for a genital examination, and the names of the intervention group will be announced to the specialist.

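### The midwife visit probably reaches only the intervention arm and is not described as part of the ISD programme, so a difference on the four primary scales could not be credited to the ISD training alone

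*Protocol article*

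**What the plan says.** Two sections of the protocol article describe a free visit involving a midwife.

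- **Strategies to improve adherence to interventions.** The section opens with "Women are required to be present at the study site in person to receive the intervention, and any missed sessions are recorded to check adherence", goes on to flexible training times, and ends with "Participants will be arranged for a free visit with a trained midwife for genital examination and health counseling". No arm is named.
- **Engagement and retention.** Here "a trained midwifery will coordinate for a genital examination, and the names of the intervention group will be announced to the specialist". Counselling is not mentioned, and nothing equivalent is stated for controls.

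Under Trial design, "the control arm will receive the training program after the final research data collection, with training from June 2023". The section on the intervention programs also gives controls their intervention after the final evaluation. No control activity during follow-up is described.

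The inference is aimed at the ISD programme. The main question under Outcome measures is "Does the educational intervention based on Instructional System Design (ISD) model affect STI preventive behaviors among Iranian women", and the Hypothesis section gives the impact of the ISD-based programme as the main aim. The primary outcomes are four scales: STI knowledge, vulnerability, prevention self-efficacy and prevention intentions. The sections that describe how the intervention is built (Phase 2, the ISD model steps, Phase 3) do not list the visit as a component.

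**The concern.** Randomisation balances the women at entry. It does not separate two things that are given to the same arm after allocation. If trained women also have a midwife contact that includes health counselling, and controls do not, the between-arm difference estimates the effect of training and visit together. The hypotheses and the main question would credit all of it to the ISD-based programme.

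Counselling by a midwife in an STI-prevention trial could plausibly move knowledge, perceived vulnerability, self-efficacy or intentions. Participants and staff are not masked, so masking gives no protection against unequal contact. What is at stake is what the trial can conclude: that the ISD training works, or that a package of training plus midwife visit works.

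**Working it through.** The documents give no figure for the visit, so the check is a comparison of the sections, followed by a short illustration with assumed values.

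**Step 1. Who is offered the visit?** The adherence section speaks of participants in general, but its subject is attendance at training, and controls have no sessions to attend before final data collection. The natural reading is the trained women. The retention section is more explicit: "the names of the intervention group will be announced to the specialist". The two sections therefore most probably agree on the intervention arm. Neither says so outright, and neither excludes controls.

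**Step 2. What does the visit contain?** The adherence section gives genital examination and health counselling. The retention section gives examination only: "for a free visit, a trained midwifery will coordinate for a genital examination". Treating these as one visit is an inference. It is supported by three shared features: the visit is free, a midwife is involved, and there is a genital examination.

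**Step 3. When does it take place?** The visible text gives no date. Its use as an adherence and retention aid suggests that it falls during the study, before the last questionnaire.

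**Step 4. What do controls get meanwhile?** Training after final data collection. Nothing else is described.

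**Step 5. What does the contrast then estimate?** Let T be the effect of training on a scale, e the effect of the visit (both in SD units), and u_I and u_C the proportions attending in the two arms before the questionnaire. Assuming the effects add:

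expected difference = T + e × (u_I − u_C)

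- Visit in the intervention arm only (u_C = 0): the difference is T + e × u_I, which is not T.
- Visit offered to both arms on the same terms, with equal uptake: the second term is zero and the difference is T.

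**Step 6. Illustration only.** The documents give neither e nor the uptake. Assume T = 0, u_C = 0, the stated 63 per group, the stated alpha of 0.05 taken as two-sided, and a two-sample t-test. The test has 126 − 2 = 124 degrees of freedom and noncentrality e × u_I × √(63/2). The chance of a significant result on one scale, which would be 5% with no shift, is:

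| Assumed e (SD) | u_I = 1 | u_I = 0.5 |
|---|---|---|
| 0.1 | 8.6% | 5.9% |
| 0.2 | 20.0% | 8.6% |
| 0.3 | 38.6% | 13.3% |

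The same calculation with 75 per group at full uptake gives about 9%, 23% and 45%. More women do not remove the shift; they make it easier to detect. The table shows how the mechanism behaves and does not estimate what this visit would do.

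**The case against.** A reader might infer that the two sections flatly contradict each other, with none of the controls getting the visit on one account and all of them on the other. The text does not support that. The adherence section is about women receiving the intervention, so its general wording fits the intervention arm. The retention section leaves counselling out without denying it, and it does not say that only the intervention group's names are passed on. This part of the objection stands. It does not remove the problem, because a visit for the intervention arm only then becomes the likeliest plan.

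A reader might also infer that intervention women get one-to-one STI counselling during follow-up while controls get nothing. Individual delivery, STI content and timing are not in the visible text, and the absence of any control contact is read from silence. The schedule table and the two figures are not shown, and a fuller protocol may give these details.

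It could be argued further that a visit given to both arms would also damage the trial. It would not. Offered on the same terms, it preserves the randomised contrast for the training, and the article never calls the control arm untreated.

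Finally, a package effect is a legitimate target in a trial that calls itself practical. That is correct, but the article does not declare a package. Its hypotheses and main question name the ISD-based programme, and its account of that programme leaves the visit out.

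**Conclusion.** The point holds as a matter of attribution. On the most natural reading, the intervention arm receives a counselling and examination contact in addition to the ISD training, and no such contact is described for controls before final data collection. A difference on the four primary scales could then not be attributed to the ISD training alone. It would still be a valid randomised effect of everything the intervention arm received.

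This rests on three assumptions: that both sections describe the same visit, that it falls before the last questionnaire, and that controls are not offered it on the same terms. If the third is wrong, the contrast for the training stands.

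The size of any counselling effect cannot be derived from the documents. A reader might take the illustrative error rates as a measure of the harm, but they depend entirely on assumed shifts and uptake and on a training effect of zero. The matter deserves correction because the change is cheap and settles what the trial may claim.

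**What to change.** 1. Reconcile the adherence section with the engagement and retention section in one statement. It should say which arm or arms are offered the visit, whether it includes health counselling, and when it falls relative to the immediate, 1-month and 3-month questionnaires. The choice of arm and content is for the sponsor.
2. Record attendance and date of the visit for each woman, in both arms.
3. If the visit is intervention-only before the last questionnaire, define the tested intervention as ISD training plus midwife visit, and word the hypotheses, main question and conclusion to match.
4. If both arms are offered it on the same terms, keep the hypotheses and describe the comparator as the visit with delayed training.

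The cost is a wording amendment and a record of attendance and date for each woman, with no extra participants. The downside is a somewhat narrower claim if the visit stays in one arm.

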### Instruments

The instrument that will be used to collect the data is the STI Four-Scale of Preventive Behaviors in females [2]. This scale was finalized by applying 40 five-point Likert response items where the items ranged from completely agree to completely disagree; the higher the score the greater the preventive STI behaviors. The calculated Content Validity Rate (CVR) and Content Validity Index (CVI) of the four-scale items ranged between 0.56–1.00 and 0.83–1.00, respectively. The impact score of all items was above 1.5. Cronbach’s alpha for each scale was as follows: STI knowledge (0.81), STI vulnerability (0.66), STI prevention self-efficacy (0.83), and STI prevention intentions (0.85). Cronbach’s alpha and intra-class correlation coefficient were calculated for the reliability of the four-scale items and ranged between 0.66–0.85 and 0.846–0.977, respectively.

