### Hypothesis

The main aim is to assess the impact of an educational program based on the ISD model on improving preventive behaviors for STIs Iranian women. Intervention effects will be examined at 4 months. The research hypotheses are as follows:The intervention group will show higher preventive behaviors for STIs than the control group measured by mean scores.The intervention group will show STI knowledge more than the control group measured by mean scores.The intervention group will show STI vulnerability than the control group measured by mean scores.The intervention group will show STI prevention self-efficacy more than the control group measured by mean scores.The intervention group will show STI prevention intentions more than the control group measured by mean scores.

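### A higher score on four scales of knowledge, vulnerability, self-efficacy and intentions is read as greater preventive behaviour; it supports a conclusion about determinants of behaviour, not behaviour

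*Protocol article*

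**What the plan says.** Under Outcome measures, the protocol article asks: "Does the educational intervention based on Instructional System Design (ISD) model affect STI preventive behaviors among Iranian women". It continues: "To answer this main question following primary outcomes are expected", and lists STI knowledge, STI vulnerability, STI prevention self-efficacy and STI prevention intentions. An effect on preventive action is then described as an expected consequence, and the measurement of it is placed lower: "To assess the expected secondary outcomes a self-reported assessment addressing preventive actions", with condom use, Pap testing and genital examination as the actions.

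The Hypothesis section has five hypotheses. The first is: "The intervention group will show higher preventive behaviors for STIs than the control group measured by mean scores". The other four take knowledge, vulnerability, self-efficacy and intentions one at a time.

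The Instruments section names one tool: "The instrument that will be used to collect the data is the STI Four-Scale of Preventive Behaviors in females". It has 40 five-point Likert items, and "the items ranged from completely agree to completely disagree". Its scales are identified with their reliability coefficients: "STI knowledge (0.81), STI vulnerability (0.66), STI prevention self-efficacy (0.83), and STI prevention intentions (0.85"). The score is interpreted as "the higher the score the greater the preventive STI behaviors".

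**The concern.** The question and the leading hypothesis are about what women do. The primary data are about what women know, how vulnerable they feel, how capable they feel and what they intend. The scoring sentence treats the second as if it were the first.

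This matters for this intervention in particular. A training programme acts most directly on knowledge and on agreement with taught statements, and the Randomization and blinding section says that participants and staff cannot be masked. Scale scores could rise with no demonstrated change in condom use or screening. If the scoring sentence is carried into the report, that result could be presented as improved preventive behaviour. The Conclusion section already describes the programme in terms of promoting behaviours that prevent infection and speaks of generalising it to women at risk.

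**Working it through.** No figure in the protocol bears on this point, so the check is to set the constructs side by side.

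| Place in the protocol article | What it refers to | Is an action measured? |
|---|---|---|
| Outcome measures, main question | Preventive behaviours | This is the target |
| Hypothesis 1 | Preventive behaviours, by mean scores | Not specified |
| Hypotheses 2 to 5 | Knowledge, vulnerability, self-efficacy, intentions | No |
| Outcome measures, primary | The same four constructs | No |
| Instruments, scales | The same four constructs | No scale named for actions |
| Instruments, response format | Agreement or disagreement | No frequency or occurrence recorded |
| Outcome measures, secondary | Condom use, Pap test, genital examination | Yes, self-reported |
| Instruments, scoring sentence | Preventive behaviours | Claimed, but not among the named scales |

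1. *Primary outcomes against the question.* Four primary outcomes are listed as answering a question about behaviour. Those that are actions: 0 of 4.

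2. *Hypotheses against primary outcomes.* There are five hypotheses and four listed primary outcomes. Hypotheses 2 to 5 match them one to one, leaving 5 − 4 = 1 hypothesis without a listed primary outcome of its own: hypothesis 1. Because behaviours are listed beside the four constructs, the protocol's own wording treats them as something different.

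3. *Instrument against the scoring sentence.* The four named scales are the four primary outcomes, with no fifth scale for actions. Any total is therefore built from those four constructs alone, and adding them together cannot introduce information about actions.

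4. *The protocol's own order of events.* Outcome measures puts the four constructs first, says that an effect on action is expected to follow, and measures action separately. That is a determinant-then-behaviour model, and the scoring sentence collapses its two steps into one.

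5. *What the action data can carry.* Three actions are named, with no stated composite. One of them is partly supplied by the trial: Strategies to improve adherence to interventions arranges a free midwife visit for genital examination, and Engagement and retention says that the specialist is told who is in the intervention group. A difference between arms in examination could therefore reflect access provided by the trial as well as changed behaviour.

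**The case against.** The best defence is that hypothesis 1 does have a measure. It is to be assessed by mean scores, and the instrument carries preventive behaviours in its title, so hypothesis 1 may well mean the total score, with hypotheses 2 to 5 as its subscales. This reading is plausible. A reader might otherwise infer that hypothesis 1 has no outcome at all, and the text does not establish that. But the total-score reading does not cure the problem: the total would contain no named action scale, and a rise in knowledge alone could raise it.

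Second, the Background cites a broad definition of health-related behaviour and its determinants that takes in beliefs, motivations and perceptions. This explains the usage. The definition nonetheless names determinants as well as behaviour, and Outcome measures keeps the two apart.

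Third, making determinants primary and self-reported action secondary is a legitimate design choice, and a rise in knowledge without a change in condom use would be visible in the planned data. This stands. A reader might infer that the trial collects nothing on behaviour, or can conclude nothing about it; neither is so. Nor does the protocol contain an explicit rule that a positive scale result is to be declared behaviour change, and its statements about generalising are conditional on the programme being effective. The objection here is to the interpretation given to the score, not to the choice of outcomes.

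Fourth, the 40 items themselves are in a cited source that is not available here, so their content is judged from the scale names and the response format. This is a limit on the check, though the protocol offers no indication that any item records an action.

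**Conclusion.** The point holds in this form: the four-scale result, total or subscale, supports conclusions about knowledge, perceived vulnerability, self-efficacy and intentions. It does not by itself support the statement that preventive behaviours improved, and the scoring sentence in Instruments is wrong to equate the two. The scale data remain valid for what they measure; what fails is the step from them to behaviour. It should be corrected because it governs the trial's headline claim.

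A reader might want to attach a number, for example by assuming how strongly intentions relate to action and computing power for the implied change in behaviour. The documents do not support this: they give no such correlation, no effect size or action rates in the text, and no continuous action score. The size is therefore stated only as 0 of 4 primary outcomes being actions. The verdict assumes that the scale names describe their items fairly.

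**What to change.** - In Instruments, replace the scoring phrase with: *greater preventive knowledge, perceived vulnerability, self-efficacy and intention*.
- Word the primary conclusions as effects on these four constructs. If hypothesis 1 means the total score, say so and word it the same way.
- Base any statement about preventive behaviours on the self-reported actions already planned. Report condom use, Pap testing and genital examination separately, as secondary evidence.
- Do not rest a behavioural statement on genital examination alone, given the visit that the trial arranges and the passing of the intervention group's names to the specialist.

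No new data are needed. Rewording a hypothesis may count as a change of objectives under the Protocol amendment section and would then need the approvals described there. The scientific cost is a narrower headline claim. The behavioural evidence would also be evidence for which the trial was not shown to be powered: the text of the sample size section gives 63 per group for a difference between groups without naming the outcome.
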